#### Severity

Adverse events will be graded by a numerical score according to the defined NCI Common Terminology Criteria for Adverse Events (NCI CTCAE) Version 5.0. Adverse events not specifically defined in the NCI CTCAE will be scored on the Adverse Event log according to the general guidelines provided by the NCI CTCAE and as outlined below.

- Grade 1: Mild
- Grade 2: Moderate
- Grade 3: Severe or medically significant but not immediately life threatening
- Grade 4: Life threatening consequences
- Grade 5: Death related to the adverse event

#### Serious Adverse Events

OHRP and UTSW HRPP define serious adverse events as those events, occurring at any dose, which meets any of the following criteria:

- Results in death
- is life-threatening (places the subject at immediate risk of death from the event as it occurred);
- Results in inpatient hospitalization or prolongation of existing hospitalization;
- Results in persistent or significant disability/incapacity;
- Results in a congenital anomaly/birth defect; or
- Based upon appropriate medical judgment, may jeopardize the subject's health and may require medical or surgical intervention to prevent one of the other outcomes listed in this definition.

Note: A "Serious adverse event" is by definition an event that meets ***any*** of the above criteria. Serious adverse events may or may not be related to the research project. A

serious adverse event determination does not require the event to be related to the research. That is, both events completely unrelated to the condition under study and events that are expected in the context of the condition under study may be serious adverse events, independent of relatedness to the study itself. As examples, a car accident requiring  $\geq 24$  hour inpatient admission to the hospital would be a serious adverse event for any research participant; likewise, in a study investigating end-stage cancer care, any hospitalization or death which occurs during the protocol-specified period of monitoring for adverse and serious adverse events would be a serious adverse event, even if the event observed is a primary clinical endpoint of the study.

Pre-planned hospitalizations or elective surgeries are not considered SAEs. Note: If events occur during a pre-planned hospitalization or surgery, that prolong the existing hospitalization, those events should be evaluated and potentially reported as SAEs.

 NCI defines hospitalization for expedited AE reporting purposes as an inpatient hospital stay equal to or greater than 24 hours. Hospitalization is used as an indicator of the seriousness of the adverse event and should only be used for situations where the AE truly fits this definition and NOT for hospitalizations associated with less serious events. For example: a hospital visit where a patient is admitted for observation or minor treatment (e.g. hydration) and released in less than 24 hours. Furthermore, hospitalization for pharmacokinetic sampling is not an AE and therefore is not to be reported either as a routine AE or in an expedited report.

#### 7.2.2 Unanticipated Problems Involving Risks to Subjects or Others (UPIRSOs):

The phrase “unanticipated problems involving risks to subjects or others” is found, but not defined in the HHS regulations at 45 CFR 46, and the FDA regulations at 21 CFR 56.108(b)(1) and 21 CFR 312.66. Guidance from the regulatory agencies considers unanticipated problems to include any incident, experience, or outcome that meets ALL three (3) of the following criteria:

- Unexpected in terms of nature, severity or frequency given (a) the research procedures that are described in the protocol-related documents, such as the IRB-approved research protocol and informed consent document; and (b) the characteristics of the subject population being studied;
- AND**
- Related or possibly related to participation in the research (possibly related means there is a reasonable possibility that the incident, experience, or outcome may have been caused by the procedures involved in the research);
- AND**
- Suggests that the research places subjects or others at greater risk of harm (including physical, psychological, economic, or social harm) than was previously known or recognized. Note: According to OHRP, if the adverse event is serious, it would always suggest a greater risk of harm.

#### Follow-up

All adverse events will be followed up according to good medical practices.

### 7.3 **Steps to Characterize a Serious Adverse Event for Reporting to the SCCC DSMC**

Step 1: Identify the type of adverse event using the NCI Common Terminology Criteria for Adverse Events (CTCAE v5.0).

Step 2: Grade the adverse event using the NCI CTCAE v5.0

**Step 3:** Determine whether the adverse event is related to the protocol therapy.

Attribution categories are as follows:

- Definite – The AE *is clearly related* to the study treatment.
- Probable – The AE *is likely related* to the study treatment.
- Possible – The AE *may be related* to the study treatment.
- Unlikely – The AE *may NOT be related* to the study treatment.
- Unrelated – The AE *is clearly NOT related* to the study treatment.

**Note:** This includes all events that occur within 30 days of the last dose of protocol treatment to the end of the acute adverse events reporting period as defined in section 7.2.1). Any event that occurs during the late adverse event period as defined in section 7.2.1) and is attributed (possibly, probably, or definitely) to the agent(s) must also be reported as indicated in the sections below.

**Step 4:** Determine the expectedness of the adverse event. Expected events are those that have been previously identified as resulting from administration of the treatment. An adverse event is considered unexpected, for expedited reporting purposes only, when either the type of event or the severity of the event is not listed in:

- the current known adverse events listed in the Agent Information Section of this protocol (if applicable);
- the drug package insert (if applicable);
- the current Investigator's Brochure (if applicable)
- the Study Agent(s)/Therapy(ies) Background and Associated Known Toxicities section of this protocol

### **7.3.1 Reporting SAEs and UPIRSOs to the Simmons Comprehensive Cancer Center (SCCC) Data Safety Monitoring Committee (DSMC)**

SAEs and UPIRSOs at all sites, which occur in research subjects on protocols for which the SCCC is the DSMC of record require reporting to the DSMC regardless of whether IRB reporting is required. All SAEs occurring during the protocol-specified monitoring period and all UPIRSOs should be submitted to the SCCC DSMC within 5 business days of the study team members awareness of the event(s). In addition, for participating centers other than UTSW, local IRB guidance should be followed for local reporting of serious adverse events or unanticipated problems.

The UTSW study PI is responsible for ensuring SAEs/UPIRSOs are submitted to the SCCC DSMC Coordinator. This may be facilitated by the IIT project manager, study team, sub-site or other designee. Electronic versions of the eIRB Reportable Event report; FDA Form #3500A forms, or other sponsor forms, if applicable; and/or any other supporting documentation available should be submitted to the DSMC.

UT Southwestern and affiliates will submit documentation via the SAE submission portal (InfoReady). The DSMC Coordinator will route the form to the DSMC Chair who determines if immediate action is required. Follow-up eIRB reports, and all subsequent SAE or UPIRSO documentation that is available are also submitted to the DSMC Chair who determines if further action is required via the same process. (*See Appendix V of the SCCC DSMC Plan for instructions on how to submit SAEs through the portal.*)

If the event occurs on a multi-institutional clinical trial coordinated by the UTSW Simmons Comprehensive Cancer Center, the IIT Project Manager or designee ensures that all participating sites are notified of the event and resulting action, according to FDA guidance for expedited reporting. DSMC Chair reviews all SAEs and UPIRSOs upon receipt from the DSMC Coordinator. The DSMC Chair determines whether action is required and either takes action immediately, convenes a special DSMC session

(physical or electronic), or defers the action until a regularly scheduled DSMC meeting.

### Reporting Unanticipated Problems Involving Risks to Subjects or Others (UPIRSOs) to the UTSW HRPP

UTSW reportable event guidance applies to all research conducted by or on behalf of UT Southwestern, its affiliates, and investigators, sites, or institutions relying on the UT Southwestern IRB. Additional reporting requirements apply for research relying on a non-UT Southwestern IRB.

According to UTSW HRPP policy, UPIRSOs are incidents, experiences, outcomes, etc. that meet **ALL three (3)** of the following criteria:

1. Unexpected in nature, frequency, or severity (i.e., generally not expected in a subject's underlying condition or not expected as a risk of the study; therefore, not included in the investigator's brochure, protocol, or informed consent document), AND
2. Probably or definitely related to participation in the research, AND
3. Suggests that the research places subjects or others at a greater risk of harm (including physical, psychological, economic, or social harm) than was previously known or recognized. Note: According to OHRP, if the adverse event is serious, it would always suggest a greater risk of harm.

UPIRSOs must be promptly reported to the UTSW HRPP within 5 working days of PI awareness.

#### Events NOT meeting UPIRSO criteria:

Events that do NOT meet UPIRSO criteria should be tracked, evaluated, summarized, and submitted to the UTSW HRPP/IRB at continuing review.

For more information on UTSW HRPP/IRB reportable event policy, see

[policy\\_9.5reportable.pdf \(utsouthwestern.edu\)](#)

#### 7.4 Stopping Rules

See statistical section 10.1 Phase I dose escalation and waiting periods.

### 8.0 MISCELLANEOUS INFORMATION

#### 8.1 Lumpectomy Guidelines

These guidelines are based on NSABP experience and implementation in previous trials with experience resulting in improved cosmesis. These guidelines are suggestions and are not mandatory for patient entry or protocol compliance.

Lumpectomy should be performed 8 to 52 weeks after XRT in a manner that achieves good cosmesis with adequate resection of the tumor with negative margins. Examples of practices leading to good cosmesis are: use of curvilinear incisions for lesions located in the upper half of the breast, use of radial incisions in the lower half of the breast, avoidance of drains in the lumpectomy cavity, separate incisions for the lumpectomy and axillary dissection.

The initial biopsy should be performed as if it was a lumpectomy; i.e., precautions should be taken to ensure that the margins of the resected tissue are grossly free of tumor thus avoiding a re-excision of breast tissue if biopsy is positive for cancer and the final margins are histologically negative. Margins are considered negative if there is no invasive or non-invasive tumor within 2 mm of the inked margin.

#### Hormonal Therapy

Endocrine therapy after pre-operative radiation should be started within 21 days after pre-operative radiation, but it is encouraged to start the day after post-radiation biopsy.

### 9.0 CORRELATIVES/SPECIAL STUDIES

Submission of samples for correlative studies is optional.

The goal of the planned laboratory correlative studies is to:

#### **Exploratory endpoints:**

- Primary tumor biopsies (pending volume of tissue)
  - Expression of PD-L1, PD-L2, PD1, CD3, CD68, CD8, Ki67.
  - RNAseq analyses including RNA profiling.
  - Whole exome sequencing to determine mutational burden and neoantigen detection.
  - T-cell receptor sequencing to determine intratumoral TCR diversity.
  - IHC to quantify immune populations.
- Blood (both Serum and PBMC)
  - T-cell receptor sequencing to determine tumor-specific TCR diversity, expansion and contraction.
  - Analysis of antibody response (both quantitative antibody titer and qualitative antibody binding and functionality).
  - Study of T-cell composition and functioning.
  - Identification of circulating antigen, DNA or tumor cells.
  - Analysis of cytokine response.
  - Analysis of blood cell composition using flow cytometry or mass cytometry.
  - Analysis of inflammatory status

## 9.1 Optional Sample Collection Guidelines

Samples will be labeled with the subject's de-identified study number and collection date.

**Whole blood and serum sample:** Patient's whole blood will be collected in four 10 mL Lavender Top EDTA tubes at baseline within 30 days prior to radiotherapy, 4 weeks after radiotherapy, and 4 weeks after surgery. In addition, 10 mL will be collected in anti-coagulant-free tubes (Red top) for the collection of serum. Approximately 50 mL of blood will be collected at each visit. The blood will immediately be processed (within 2 hours) by centrifugation (1000g, 15min, 4°C), collecting the supernatant and freezing at -80°C in 5 aliquots for future experiments. The pellet will be re-suspended in PBS and PBMC will be isolated using standard protocol. Briefly, the cell suspension will be carefully placed on 10mL polystyrene tube containing 1ml ficoll and centrifuged (400g, 30min, RT). Collect the PBMC region from the ficoll and washed 3x with PBS. Count and freeze cells in 5 aliquots with 10%DMSO 90%FBS in -80oC.

Optional Blood samples at each time point of 30 days prior to XRT, 4 weeks after XRT, and 4 weeks after surgery (see Section 5.4 for sample collection windows):

- 4 10 mL Lavender top tubes (whole blood)
- 1 10 mL Red top tube (serum)

**Tumor Sample:** An image-guided biopsy of tumor lesion consisting of 4-5 18G needle cores is recommended at the time of tissue diagnosis. If the patient participated in protocols such as the Pathology Tissue Repository Protocol or procedures and the tissue confirming breast cancer diagnosis is in storage and available at UTSW Medical Center or an outside institution, the study team may request a tissue sample. The study team will also request frozen and formalin-fixed paraffin embedded (FFPE) samples from surgical specimen. These samples may be used for generation of tumor lysates (which can be used as source of antigens for immunoassays). The samples may also be used for a variety of assays, including but not limited to ELISA, Elispot assay, H-thymidine Proliferation Assay, Chromium Release Cytotoxicity Assays, Flow cytometric analysis (FACS), Immunohistochemical staining (IHC), Serum Cytokine Analysis and Western-blot/Immuno-blot analysis. DNA and RNA sequencing may be performed and de-identified sequence may be submitted to publicly accessible databases as required by journal or institutional requirements

## 9.2 Specimen Banking

Subject samples collected for this study will be retained at the UTSW Radiation Oncology biorepository. Specimens will be stored indefinitely or until they are used up. If future use is denied or withdrawn by the subject, best efforts will be made to stop any additional studies and to destroy the specimens.

[name] MD/PhD or [name], PhD will be responsible for reviewing and approving requests for clinical specimen from potential research collaborators outside of UTSW. Collaborators will be required to complete an agreement (a Material Transfer Agreement or recharge agreement) that states specimens will only be released for use in disclosed research. Any data obtained from the use of clinical specimen will be the property of UTSW for publication and any licensing agreement will be strictly adhered to.

The specimens, DNA, and their derivatives may have significant therapeutic or commercial value. The Informed Consent form contains this information and informs the subject that there is the potential for financial gain by UTSW the investigator or a collaborating researcher or entity.

The following information obtained from the subject's medical record may be provided to research collaborators when specimens are made available:

- Diagnosis
- Collection time in relation to study treatment
- Clinical outcome – if available
- Demographic data

## 10.0 STATISTICAL CONSIDERATIONS

### 10.1 Study Design/Study Endpoints

#### Primary Endpoint

The primary endpoint of the phase I portion is to either reach the maximum tolerated dose (MTD) or a dose of 38 Gy total (whichever comes first) by escalating the dose of SBRT toward the tumorcidal dose of 38 Gy in fraction. Patients will be treated in cohorts of seven to fifteen. Toxicity will be graded using the NCI Common Toxicity Criteria for Adverse Events (CTCAE) v. 5.0. ***A dose-limiting toxicity (DLT) is a grade 3 toxicity deemed definitely related to treatment in the following categories: skin, rib bone (fracture), pulmonary (radiation pneumonitis), or neurological (intercostal or brachial plexus nerves) or any grade 4 or 5 toxicity deemed definitely attributed to the therapy.*** All reported DLTs will be verified by study chair, data and safety monitoring committee, and, as appropriate, independent review before final determination that a DLT has in fact occurred. Doses will be escalated an additional 3.5-4 Gy per treatment. The phase I portion of the study will be completed when either of the following events occur: 1) the MTD for a cohort is reached or 2) when delivery of a pre-determined highest dose of radiation (38 Gy) that has been deemed likely to be efficacious for treatment of early stage breast cancer is attained.

#### Secondary Endpoints

Secondary endpoints for the phase I portion of this study include cosmetic outcome as evaluated by patient and physician. In addition, the following endpoints will be evaluated as secondary endpoints:

- Local Control
- Acute Toxicity (90 Days)
- Late Toxicity (24 months)
- Rates of Surgical Morbidity
- Pathologic Complete Response Rates
- Patient and Physician Cosmesis Outcomes
- Distant Disease-Free Survival

#### **A “Therapeutic” Phase I Trial**

Most (not all) oncology-related drug discovery phase I trials are non-therapeutic. In fact, the drug doses being studied has often never been used in humans for the stated indication. Therefore, the dose used may be wholly ineffective at providing efficacy to the patient. Second, the typical drug discovery phase I trial focuses primarily on toxicity dose response, with no formal plan to evaluate efficacy. In this context, it is assumed that the optimal dose will be the maximum tolerated dose. Neither assumption is true for the radiotherapy used in this phase I trial. Since radiotherapy is well known to provide efficacy,

even the starting dose of this trial, this phase I trial is a therapeutic trial. Furthermore, the maximum tolerated dose may or may not be the most ideal dose balancing benefit and toxicity with the widest therapeutic window. While the primary endpoint and statistical design focuses on toxicity, efficacy information regarding tumor response/control will be collected (see below).

#### Phase I Dose Escalation

The phase I study is designed to end if the rate of DLTs within 90 days from the start of treatment is 33% or higher. For each dose level cohorts, a total of seven to fifteen patients will be enrolled. If zero out of the first seven with 90 day follow-up, two or fewer out of the first nine with 90 day follow-up, three or fewer out of the first twelve with 90 day follow-up, or four or fewer out of the first fifteen of patients with 90 day follow-up experience a DLT as defined above, then the dose will escalate to the next dose level. If three or more of the first nine patients, four or more of the first twelve, or five or more of the first fifteen patients experience a DLT, then the MTD will be considered to have been exceeded. The MTD will be defined as the immediately previous lower dose level tolerated.

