## STUDY SCHEMA

### Phase I Study of Pre-Operative Stereotactic Partial Breast Irradiation Therapy for Early Stage Breast Cancer

[figure not shown]

\*\*Of note, after pre-operative radiation and prior to surgery, patients should start endocrine therapy within 21 days after pre-operative radiation but it is encouraged to start the day after post-radiation biopsy.

Prescription will be 30 Gy to the Planning Target Volume (PTV) for all dose cohorts, and either 30 Gy, 34 Gy, or 38 Gy to the GTV/CTV per appropriate dose cohort.

Number of patients= between 7-60 for phase I (depending on tolerance)

All patients in each dose cohort will be treated as a single group for dose escalation. The starting dose for the dose escalation portion will be 30 Gy. Subsequent cohorts of patients will receive an additional 4 Gy per treatment. If significant toxicity is encountered at the starting dose, a de-escalation will occur (step -1) to 26.5 Gy. As we are currently concluding an adjuvant single fraction phase I protocol (ClinicalTrials.gov Identifier: NCT02685332) to 30 Gy in a single fraction for early stage breast cancer, if we meet our endpoints of this study, we will start our dose escalation at 34 Gy instead of the 30 Gy, as safety of the 30 Gy arm will have already been established.

| Level | Dose    | No. of Patients |
|-------|---------|-----------------|
| -1    | 26.5 Gy | 7-15            |
| 1     | 30 Gy   | 7-15            |
| 2     | 34 Gy   | 7-15            |
| 3     | 38 Gy   | 7-15            |

- Prescription will be a minimum of 27 Gy to the PTV for all dose cohorts, and either 30 Gy, 34 Gy, or 38 Gy to the GTV/CTV per appropriate dose cohort. See section 4.1.5

Minimum waiting periods will be assigned between each dose cohort to evaluate toxicity. The phase I study will be completed when dose limiting toxicity is reached or when delivery of a pre-determined highest dose of radiation (38 Gy) that has been deemed likely to be efficacious for treatment of early stage breast cancer is attained.

At the time of writing this protocol, the current single fraction trial being tested in the adjuvant setting for early stage breast cancer is 30 Gy in 1 fraction at UTSW (NCT02685332). If we meet our accrual goal and waiting period without a dose limiting toxicity by the time this protocol is ready to go live, we will start our dose for this trial at 34 Gy.

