#### Technical Factors

The Cyberknife system® with its 6 MV linear accelerator will be required for radiation delivery by the protocol, MR Linac, or the Gammapod which delivers radiation with cobalt sources. Other treatment delivery options will not be considered.

**4.1.1 All patients in each dose cohort will be treated as a single group for dose escalation. The starting dose for the dose escalation portion will be 30 Gy. Subsequent cohorts of patients will receive an additional 3.5-4 Gy per treatment. If significant toxicity is encountered at the starting dose, a de-**

escalation will occur (step -1) to 26.5 Gy. If at the time of this trial opening, we have completed our ongoing adjuvant single fraction stereotactic partial breast irradiation trial dose cohort 30 Gy, and have deemed its safe, we will skip the 30 Gy arm and start at 34 Gy for this trial. Based on modeling from the universal survival curve, 38 Gy in 1 fraction is roughly biologically equivalent to the dose of 70 Gy which is the dose commonly used to treat gross disease.

| Level | Dose    | No. of Patients |
|-------|---------|-----------------|
| -1    | 26.5 Gy | 7-15            |
| 1     | 30 Gy   | 7-15            |
| 2     | 34 Gy   | 7-15            |
| 3     | 38 Gy   | 7-15            |

Prescription will be minimum of 27 Gy to the PTV for all dose cohorts, and either 30 Gy, 34 Gy, or 38 Gy to the GTV/CTV per appropriate dose cohort.

Minimum waiting periods will be assigned between each dose cohort to evaluate toxicity. The phase I study will be completed when dose limiting toxicity is reached or when the highest protocol dose of 38 Gy, which the investigators have determined to be likely efficacious in controlling gross disease, is achieved and tolerated.

At the time of writing this protocol, the current single fraction trial being tested in the adjuvant setting for early stage breast cancer is 30 Gy in 1 fraction at UTSW (clinical trials.gov number NCT02685332). If we meet our accrual goal and waiting period without a dose limiting toxicity by the time this protocol is ready to go live, we will start our dose for this trial at 34 Gy rather than 30 Gy.

Treatment can be done on MR Linac, the Gammapod or Cyberknife.

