#### **4.1.5 Radiation Planning and Target Goals for MR LINAC, Gammapod and Cyberknife:**

- 95% of the PTV should receive a minimum of 27 Gy and 99% of the target volume (GTV) receives a minimum of 93% of the prescription dose. Minor deviation if 90% of PTV receives 27 Gy. All efforts should be made to meet the skin constraint even if PTV coverage will be compromised. In this situation, would prioritize skin, brachial plexus, and spinal cord constraint over PTV coverage and this is acceptable and not a deviation, and will not be deemed a protocol violation if PTV coverage not met in order to meet these OAR constraints. Efforts should be made to keep the PTV volume coverage to a minimum dose of 27 Gy to 95% of volume. In the situation when the GTV is close to skin, prioritize the skin constraint over GTV coverage.
- Max hot spot < 130% of the prescription dose is recommended
- Prescription will be either 30 Gy, 34 Gy, or 38 Gy to the GTV/CTV per appropriate dose cohort.

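### Section 10.1 has no step-down branch for a failed starting dose, although the schema and 4.1.1 provide level -1 (26.5 Gy), and the dose at level -1 is specified incoherently

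*Protocol*

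**What the plan says.** **Step-down.** The Study Schema states: "If significant toxicity is encountered at the starting dose, a de-escalation will occur (step -1) to 26.5 Gy". Section 4.1.1 repeats this ("escalation will occur (step -1) to 26.5 Gy"). Neither gives a count, rate or grade as the trigger. Both dose tables list level -1 with 7-15 patients.

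**Stopping.** Section 7.4 consists of one pointer: "See statistical section 10.1 Phase I dose escalation and waiting periods". Section 10.1 says the phase I study is "designed to end if the rate of DLTs within 90 days from the start of treatment is 33% or higher". It treats a level as above the MTD if DLTs occur in "three or more of the first nine patients, four or more of the first twelve, or five or more of the first fifteen", and then: "The MTD will be defined as the immediately previous lower dose level tolerated". It does not mention level -1 or de-escalation. Section 11.4.3 mentions de-escalation only for the timing of a toxicity review.

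**Dose specification.** Section 4.1.1 states: "Prescription will be minimum of 27 Gy to the PTV for all dose cohorts". The GTV/CTV prescriptions listed in the schema, 4.1.1 and 4.1.5 are 30, 34 and 38 Gy only. The planning goal in 4.1.5 is "95% of the PTV should receive a minimum of 27 Gy and 99% of the target volume (GTV) receives a minimum of 93" per cent of the prescription dose, and 4.1.6 repeats it. A separate sentence near the top of the schema prescribes 30 Gy, not 27 Gy, to the PTV in every cohort.

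**The concern.** This is the safety branch of the trial's only primary endpoint. If the first level meets the 10.1 counts, the schema and 4.1.1 point to a new cohort at 26.5 Gy. Section 10.1, taken alone, points to the end of the study. With a 30 Gy start it would also leave the MTD undefined, because no lower level has been treated in this trial. Section 10.1 does not say that level -1 opens, that it can become the MTD, or what is reported if it fails too.

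If level -1 did open, its plan would be drawn under a PTV minimum written for the higher levels. The grade 3 DLT categories are skin, rib, lung and nerve, all normal tissue outside the tumour. A step-down that leaves the PTV minimum where it was does not lower the dose floor in the margin next to that tissue.

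**Working it through.** **1. The plan's own figures.** The cap of 60 (10.2) equals 4 levels (-1, 1, 2, 3) x 15 = 60. Level -1 is therefore counted as a real cohort. The 10.1 counts are 3/9 = 4/12 = 5/15 = 33.3%, which matches the 33% end rule. The event that ends the study in 10.1 is thus the same event as failure of the starting level.

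**2. What each text says when a 30 Gy start meets those counts.**

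| Question | Schema and 4.1.1 | 10.1 (via 7.4) |
|---|---|---|
| Trigger | significant toxicity, undefined | 3/9, 4/12 or 5/15 |
| Next step | open 26.5 Gy | study designed to end |
| MTD | not stated | previous lower level tolerated; none tested in this trial |
| If 26.5 Gy also fails | not stated | not stated |

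**3. How often the branch is reached.** The protocol gives no expected DLT rate, so the true rate p is an assumption. At the nine-patient look,

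P(X >= 3) = 1 - sum over k = 0, 1, 2 of C(9,k) p^k (1-p)^(9-k).

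At p = 0.10 this is 1 - (0.3874 + 0.3874 + 0.1722) = 0.053. The option to escalate on 0/7 does not alter this, because 0/7 allows at most 2/9.

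| Assumed p | >=3 of 9 | >=4 of 12 | >=5 of 15 |
|---|---|---|---|
| 5% | 0.8% | 0.2% | 0.06% |
| 10% | 5.3% | 2.6% | 1.3% |
| 20% | 26% | 21% | 16% |
| 30% | 54% | 51% | 48% |

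Each column is the chance if the decision is taken at that sample size.

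The experience cited in 1.2 is 1 DLT in 75 analyzable patients (1.3%, exact 95% CI 0.03-7.2%; five-fraction adjuvant), 1 in 25 (4%, exact 95% CI 0.1-20.4%; three-fraction preoperative with chemotherapy) and 0 in 32 (single-fraction preoperative, 15-21 Gy). None of it is single-fraction preoperative treatment at 30-38 Gy, so it does not fix p.

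**4. Dose at each level.** PTV minimum 27 Gy; GTV floor = 0.93 x level dose.

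| Level dose (Gy) | 27 Gy as % of level dose | GTV floor (Gy) |
|---|---|---|
| 26.5 | 27/26.5 = 101.9% | 24.6 |
| 30 | 90.0% | 27.9 |
| 34 | 79.4% | 31.6 |
| 38 | 71.1% | 35.3 |

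Only at level -1 does the PTV minimum exceed both the level's own dose (by 0.5 Gy) and the GTV floor. Under the other schema sentence the PTV dose would be 30/26.5 = 113.2% of the level dose.

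**5. A 34 Gy start.** Read literally, the schema and 4.1.1 step from 34 to 26.5 Gy, a drop of 7.5 Gy that passes over 30 Gy.

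**The case against.** **The two rules can be read together.** The schema and 4.1.1 can be taken as the specific rule for the starting dose and 10.1 as the general rule that supplies the counts. A tolerated level -1 would then be the MTD. The dose tables, the cap of 60 and 11.4.3 all support that intention. DLTs are also verified by the study chair and the DSMC, so an accidental closure is improbable. A reader might infer that the protocol gives irreconcilable orders. It does not. What stands is that nothing in the text makes this link, the trigger is undefined, and 10.1 speaks of the study ending, not of escalation ending.

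**Level -1 is deliverable.** A reader might infer that it cannot be planned at all. The documents do not support that. A 27 Gy PTV dose lies below 105% of 26.5 Gy (27.8 Gy) and well below the recommended 130% hot-spot limit (34.5 Gy). The GTV lies inside the PTV, so a lower GTV floor is merely slack. The PTV goal also yields to skin, brachial plexus and cord limits. A PTV minimum common to all cohorts is partly a stated design choice. What stands is incoherence: the margin must receive more than the level's nominal dose, and that dose is missing from the prescription lists.

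**The 34 Gy start.** A reader might call the jump past 30 Gy an error. The schema says the safety of 30 Gy would by then have been established in the adjuvant trial, so which level should follow is the sponsor's decision.

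**The branch is rare.** At a true rate of 5% it is reached in under 1% of trials. That limits the weight of the point but does not remove it, since a safety rule has to be clear before it is needed.

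**Conclusion.** The point holds as a gap between sections and an incoherent dose specification. Section 10.1 is wrong as written for a failed 30 Gy start: followed literally, it ends the trial without opening a cohort that the design plans and counts, and with no MTD defined. Level -1 is missing from the prescription lists, and its PTV minimum is 0.5 Gy (1.9%) above its own dose, so de-escalation would leave that minimum unchanged. The 30 Gy PTV sentence in the schema adds to the conflict.

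The chance of needing the branch at the nine-patient look is 0.8%, 5.3% and 26% at true DLT rates of 5%, 10% and 20%. Those rates are assumptions. The missing branch and the dose figures need no assumption. The sponsor should fix this. It casts no doubt on the DLT counts or the sample-size cap.

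**What to change.** 1. **Schema and 4.1.1:** replace the undefined trigger with the 10.1 counts (>=3/9, >=4/12 or >=5/15).
2. **10.1:** state that meeting these counts at a 30 Gy start opens level -1 under the same counts instead of ending the study; that level -1 is the MTD if tolerated; and that if level -1 also meets the counts, the study ends with no MTD established.
3. **Schema, 4.1.1, 4.1.5 and 4.1.6:** add 26.5 Gy wherever prescriptions are listed, and set a level -1 PTV minimum no higher than 26.5 Gy, with the value chosen by the sponsor's physicists. Delete or correct the schema sentence that prescribes 30 Gy to the PTV in every cohort.
4. **Sponsor decision, separate from the wording correction:** state which level follows a failed 34 Gy start.

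**Cost.** Items 1-3 are a short amendment plus one physics decision, with no new visits or data items and no change to the DLT counts. A failed 30 Gy start followed by level -1 uses at most 15 + 15 = 30 patients. If the sponsor chose 34, then 30, then 26.5 Gy under item 4, the maximum would be 3 x 15 = 45. That choice could add a 30 Gy cohort of 7-15 patients and its 90-day wait. Both totals stay within the cap of 60.
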